##### Maternal urine specimen collection

Urine sample will be collected from the same sub-sample as above at enrollment and 32 weeks of pregnancy to see how the level of choline metabolites differ in the four arms compared to the one receiving an extra daily dose of choline.

##### Maternal stool specimen collection

Stool specimen on the same sub-sample of 50 pregnant women per arm will also be collected at 19 and 32 weeks of pregnancy. The specimens will be assessed for inflammatory biomarkers in the stool, such as calprotectin (μg/g), lipokalin-2 (pg/ml), and myeloperoxidase (MPO), using ELISA. Furthermore, the stool samples will also be analyzed for enteropathogens using the TaqMan Array Card (TAC) system for polymerase chain reaction (PCR), which will be performed in the Infectious Disease Research Lab (IDRL). Moreover, a targeted Bifidobacterium identification will be performed using real-time PCR at IDRL. The stool samples will be sent to the University of Stanford after signing the material transfer agreement (MTA) for additional metagenomic and microbiome analyses.

#### Biomarker assessment during pregnancy period

##### Cord blood collection

On the group of the same sub-sample as above, cord blood will be collected within 30 min of birth using dried blood spot (DBS) cards to assess micro- and macronutrients and antibody status in the cord blood.

##### Breast milk collection

Colostrum from the same women will be collected within 72 h of birth to assess the quality and composition of breast milk in terms of macro- and micronutrients, including oligosaccharides, immunoglobulins, and microbiome. The analysis of breast milk specimens will be performed in the [name] Lab at the University of Manitoba. A material transfer agreement (MTA) will be developed with the University of Manitoba for the shipment of the specimens.

##### Maternal and infant stool specimen collection

Stool specimen on the same sub-sample of 50 mother-infant dyad per arm will also be collected at 1–2, 3–4, 5–6, and 12 months of infantile age. Specimens will be assessed for inflammatory biomarkers in the stool, such as calprotectin (μg/g), lipokalin-2 (pg/ml), and myeloperoxidase (MPO), using ELISA. Furthermore, the stool samples will also be analyzed for enteropathogens using the TaqMan Array Card (TAC) system for PCR, which will be performed in the Infectious Disease Research Lab (IDRL). Moreover, a targeted Bifidobacterium identification will be undertaken using real-time PCR at IDRL. The stool samples will be sent to the University of Stanford after signing the material transfer agreement (MTA) for additional metagenomic and microbiome analyses.

##### Blood specimen collection

From the same 50 mother-infant dyads per arm, infantile blood specimens will also be simultaneously collected at 1–2, 3–4, 5–6, and 12 months of infantile age for metabolomic work using Volumetric Absorptive Microsampling (VAM). The specimens will be stored in − 80 °C freezers at the IDRL and NRL storage areas of the Aga Khan University for further analysis in future research for an indefinite time. The samples will be color-coded by the type of specimen as part of a unique identification system and de-identified with barcodes, specific IDs for different time points, and mother-infant dyad information. All the ethical aspects pertaining to the storage of these samples have been approved by the Ethics Review Committee at the Aga Khan University.

### Monitoring and quality assurance

A specific team from the Aga Khan University, with expertise in data management and trial implementation working with the investigators, will be responsible for auditing the general data trial processes and training the research staff and outcome assessors to ensure the completeness and accuracy of the protocols. Moreover, the Technical Advisory Group (TAG) comprising of international experts will be evaluating the trial progress and independent experts will visit the catchment periodically for monitoring. A mechanism has also been developed for the research teams to report key progress indicators on a weekly basis to the investigators at the VITAL Pakistan Trust and Aga Khan University. Furthermore, an astringent quality assurance mechanism has been developed through which 10% of randomly selected data will be checked by trial supervisors and associates. The anthropometric measurements will be standardized, and the team members will be trained by WHO-trained master trainers. Comprehensive training and refreshers will be conducted on a routine basis for the research team members, all of whom have received Good Clinical Practice certifications.

### Data safety and monitoring board

The independent group of experts, comprising of 5 members, constitutes the Data Safety and Monitoring Board (DSMB) for the trial and are responsible for monitoring safety indicators, adverse events, and results of the interim analysis. The interim analysis (blinded by arm) is scheduled for when 50% of the enrolled participants complete the 6-month follow-up. Only DSMB members will have access to the results of interim analysis, which will be shared by the independent statistician. Data on severe adverse events will be shared with the board on a monthly basis in the form of a progress report.

### Participant safety

Close follow-up will be performed to ensure participant safety, and pregnant women will be referred to physicians at the primary health care clinic if needed, with facilitated referral to tertiary hospitals when required. An independent DSMB will monitor the safety of the study participants and practice trial oversight. Monthly reports on severe adverse events will be shared with DSMB, and when a safety red signal is observed, DSMB may stop this trial prior to the completion of recruitment. The safety net, including facilitated referral and reporting, is believed to minimize the chances of harm to participants.

### Possible risks

Trial participants may experience diarrhea, nausea, vomiting, skin rash, and abdominal distension after BEP supplementation and/or following azithromycin, nicotinamide, or choline doses. Information of all adverse event occurrences at each follow-up will be collected systematically via exhaustive history-taking for any illness since the past visit and assessing signs of concern at each visit. If the pregnant women are considered to have any concerning sign or symptom, a referral mechanism has been put in place. A 24/7 active contact number will be provided to the participants to report any serious illness, for which immediate referral will be arranged. This information will be well-documented and recorded under the “severe adverse events” field. For reporting to the ethics committee and DSMB, “severe adverse events” has been divided into two main categories: “fatal events” that may be occurring regardless of the underlying cause, and “non-fatal events” that may require hospitalization or injectable therapy during the follow-up period. Risk management includes prevention through rigorous follow-ups, and continuous monitoring, documentation, and prompt referrals for danger signs. Every illness or danger sign reported or identified is addressed through facilitated referral for both women and infants.

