### Interventions

In the control arm, standard of care, i.e., ANC care, nutritional counseling, health promotional messages of exclusive breastfeeding, and care for intrapartum and postnatal care will be disseminated to all pregnant women. In “Intervention arm 1,” in addition to the standard of care, 2 sachets of BEP supplements per day from enrolment till birth outcome will be allocated to each woman by a trained research team member at initial and subsequent follow-up visits. BEP is a certified product of the World Food Program and is locally produced by the Ismail Industries in Karachi. The manufacturers have no role in any part of the study. Each sachet contains a caloric value of 400 kcal per 75 g and approximately 10.5 g of protein. The sources of protein are mainly chickpea, peanuts, lentils, legumes, and skimmed milk. In “Intervention arm 2,” the same standard ANC counseling BEP interventional doses will be administered to each participant in addition to 2 prophylactic doses of azithromycin tablets 2 g orally at weeks 20 and 28 of gestation (window period of 7 days). In “Intervention arm 3” lastly, daily single doses of nicotinamide 100 mg orally and choline 450 mg orally will be dispensed to each pregnant woman in addition to the same standard of care plus BEP diet supplements. Provision of all ANC services as well as referral for any complication(s) during pregnancy and intrapartum period will be undertaken for all arms. Provision of all ANC services as well as referral for any complication(s) during pregnancy and intrapartum period will be undertaken for all arms. There will be no alternation to the usual care pathways (including use of any medication) and these will continue for all trial arms. All other non-study treatments, such as medications and supplements, will be recorded at each follow-up in all arms. In case any severe illness or adverse event is reported or observed, the intervention may be paused or stopped for a limited period after the investigators and the Data Safety and Monitoring Board are consulted.

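### The stated definition of a reportable severe adverse event omits a congenital anomaly in a live-born infant that is not fatal and would not require hospitalisation or injectable therapy

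*Protocol article*

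**What the plan says.** The definition is in the Possible risks section. "For reporting to the ethics committee and DSMB", severe adverse events fall into two main groups. The first is fatal events "that may be occurring regardless of the underlying cause". The second is non-fatal events "that may require hospitalization or injectable therapy during the follow-up period".

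The Data safety and monitoring board section describes what the board receives: "Data on severe adverse events will be shared with the board on a monthly basis in the form of a progress report". The Participant safety section repeats the monthly report and lets the board stop the trial early on a safety signal. The board's remit is wider. It is "responsible for monitoring safety indicators, adverse events, and results of the interim analysis".

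Collection is also wider than reporting: "Information of all adverse event occurrences at each follow-up will be collected systematically via exhaustive history-taking for any illness since the past visit". Infants are included in clinical follow-through: "Every illness or danger sign reported or identified is addressed through facilitated referral for both women and infants".

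On exposure, the Interventions section gives all three active arms "2 sachets of BEP supplements per day from enrolment till birth outcome". Arm 2 adds azithromycin at weeks 20 and 28, and arm 3 adds daily nicotinamide and choline.

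**The concern.** The reporting rule depends on death or on the treatment an event may need. That suits intercurrent illness in the mother. It suits a structural finding in the newborn less well, because such a finding can matter for safety without needing admission or an injection. The article nowhere mentions congenital anomaly, malformation or birth defect, so nothing else in it brings such a case into the report.

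At stake is the completeness of the safety account for the exposed infant. Staff who follow the rule as written have no instruction to report such a case. The board could then review the monthly reports without those cases, and a final safety table built from reportable events would omit them too.

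**Working it through.** The article gives no figure to reproduce. The check is to follow a case through the stated rules.

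**1. Is there fetal exposure?** Yes, in three of four arms. Enrolment falls between just over 8 and just under 19 weeks, and BEP runs from enrolment to birth. Nicotinamide and choline are taken daily in arm 3. Azithromycin in arm 2 is given only at weeks 20 and 28, so exposure from enrolment should not be attributed to that drug.

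**2. Which anomalies are reportable as the text stands?**

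| Infant with an anomaly | Fatal category | Non-fatal category | Reportable |
|---|---|---|---|
| Dies | yes | – | yes |
| Survives, may require hospitalisation or injectable therapy | no | yes | yes |
| Survives, would require neither | no | no | no |

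Neither category is limited to mothers, so the first two rows are covered. The criterion is that treatment may be required, not that it was given. An anomaly that could need admission therefore qualifies whether or not admission happens. Only the third row is the gap.

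**3. Does another stated route bring the third row to the DSMB?**
- *Adverse-event collection.* All adverse events are collected by history-taking and by looking for signs of concern. This may pick up an anomaly, but no onward route to the board is given for events that are not severe.
- *Board remit.* It includes adverse events and safety indicators. The indicators are not defined, and the only routine feed described is the monthly report.
- *Interim analysis.* Its timing is stated (half of the enrolled participants past the 6-month follow-up), but its safety content is not.
- *Pausing the intervention.* The Interventions section has the board consulted when an event leads to a pause. That concerns treatment in pregnancy, which has ended by the time an anomaly is seen in a live-born infant.

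No explicit route remains.

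**4. Can the gap be sized?** The number of infants in it is N × p × f. N is births assessed, p is the prevalence of recognisable anomaly, and f is the fraction of anomalies that meet neither category.
- N from the Sample size section: 1884 × (1 − 0.21) = 1488. With the abstract's 1836: 1836 × 0.79 = 1450.
- p is not in the documents. If it is assumed to be 1% to 3%, then 1488 × 0.01 = 15 and 1488 × 0.03 = 45, or about 4 to 11 per arm. These are all anomalies, including those already reportable.
- f is not in the documents and could lie anywhere from 0 to 1.

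With f unknown, the count in the gap could be anything from none to the whole total, so no size is claimed.

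**The case against.** The strongest case against is that this is a condensed article. An active full protocol, version 1.6, is cited but not shown. Sub-definitions of severe adverse events and the items on the birth form would normally sit there, and the article lists its case report forms by domain only. That stands as far as it goes: the absence of anomalies from the list of form domains or from Table 2 proves nothing, and this point does not rely on it. What remains is that the article itself states the reporting definition and states it narrowly. Calling the two categories main ones leaves room for others, but none is named.

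A reader might infer several stronger claims that the documents do not support:
- *No harm first seen in a newborn is reportable.* A neonatal death or an event that may need admission fits the stated categories.
- *Only anomalies actually treated in hospital or by injection count.* The wording is wider than that.
- *The board will certainly receive no count, or the final report cannot give one.* Adverse events are collected and lie within the board's remit. What is missing is a stated route, which is less than a bar.
- *Some 15 to 45 infants would go unreported.* That range rests on an assumed prevalence and counts all anomalies.

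Timing also limits the point. Recruitment was due to finish in January 2022, the month of publication, so little remained of any decision to stop enrolment. Infant follow-up to December 2023 and database lock in June 2024 still left room for monitoring and for the final safety table.

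**Conclusion.** The point holds in limited form. By the article's own wording, a congenital anomaly in a live-born infant that is not fatal and would not require hospitalisation or injectable therapy falls outside what is reported to the ethics committee and the DSMB. Anomalies that meet either criterion are inside. The residue may consist largely of less serious anomalies, and its number cannot be derived from the documents. The conclusion assumes that the two stated categories are the working rule and that the full protocol does not widen them. It makes no claim that any study product causes anomalies. It bears on the safety account only. Birth weight, the sample size and the efficacy analysis are unaffected.

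**What to change.** In the Possible risks section, add a third reportable category: congenital anomaly, whatever treatment is given. If the full protocol already has it, bring the article's definition into line.

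Record visible or reported anomalies through the follow-up and adverse-event contacts already made with the mother-infant dyad. Do not add this to the 72-hour birth assessment: the Blinding section restricts those assessors to anthropometry, and the training described for them is in anthropometry. For infants already born, the remaining visits up to 11 to 12 months can be used.

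Include counts by coded arm in the monthly DSMB report, in keeping with the blinded interim review, and in the final safety table.

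The cost is slight: one category, one form item and a few more lines in a report already sent. There are two limits to state when reporting. Visible or reported anomalies will be ascertained incompletely, so the counts are minimum figures. The follow-up teams also hand out the supplements and so can know the arm, which means recording may differ between arms. The counts suit descriptive safety review, not formal testing.

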### Statistical analysis

All analyses will be done using Stata software version 16. Descriptive analysis of each group will be conducted, and percentages or continuous data with SD will be reported. The baseline characteristics will be assessed by arm. The primary approach will be intention-to-treat (ITT) analysis to compare primary and secondary growth outcomes. Mean differences will be assessed using one-way ANOVA, with the model adjusted for baseline characteristics including maternal age, BMI, gestational age, gravidity, MUAC, and newborn age at birth assessment. Key assumptions are that outcome data will be repeatedly measured, normally distributed, and following the superiority principle. For covariate analysis, both the unadjusted and stepwise-adjusted models will be run. Point estimates less than 10% will be reported as unadjusted despite of the model employed. Potential sub-group analyses for primary and secondary outcomes will be based on infantile gender and maternal data at enrolment, i.e., MUAC < 21.0 cm or ≥ 21.0 cm, age < 30 years or ≥ 30 years, gravidity < 3 or ≥ 3, and BMI < 18.5 kg/m^2^ or ≥ 18.5 kg/m^2^.

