## Methods

### Trial design

This is a multi-arm community-based randomized controlled, open-label, assessor-blinded superiority trial with a treatment allocation ratio of 1:1:1:1. A multi-arm trial was selected to determine the incremental impact of BEP to the pregnant woman, along with two doses of oral azithromycin or oral daily nicotinamide and choline on birth weight. This protocol has been developed in accordance with the guidelines set forth by Standard Protocol Items: Recommendations for Interventional Trials (SPIRIT) [26].

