### Sample size

The sample size is calculated via permutation and subsequent adjustment for three comparisons between arms, i.e., intervention arms with control. Improved perinatal outcomes are hypothesized with the supplement of BEP alone or co-administration of BEP supplement with azithromycin as well as with nicotinamide and choline. Thus, the sample size estimated per arm is based on 1-tailed hypothesis testing of birth weight as the primary outcome, a significance level of 2.5% to account for multiple comparisons, and initial assumption of dropout proportion of 21% of study participants assumed in the trial. For birth weight (the primary outcome), it is assumed that the mean difference will be at least 100 g [30]. In order to achieve a test power of 80% and maintain family-wise error rate (FWER) of 0.05; Bonferroni method for three comparisons, alpha of 0.017, and an estimated sample size of 370 pregnant women per arm was attained. A 21% dropout rate was thereafter considered on account of miscarriages, stillbirths, early neonatal deaths, losses to follow-ups, and missed birth assessments due to varying on-field challenges owing to the pandemic. Hence, the sample size was thereafter adjusted to 471 pregnant women in each arm making up a total of 1884 pregnant women for this trial.

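### The analysis section names a one-way ANOVA without linking it to the three control comparisons at 0.017 on which the trial is sized, so the text does not secure the stated family-wise error rate.

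*Protocol article*

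**What the plan says.** The Statistical analysis section of the protocol article gives the method for the primary and secondary growth outcomes under intention to treat: "Mean differences will be assessed using one-way ANOVA", in a model with covariates. It then lists the covariates and says that unadjusted and adjusted models will both be run. It names no contrasts, test level or sidedness for birth weight, and does not refer back to the sample size rule.

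The Sample size section describes a different structure. The calculation involves "subsequent adjustment for three comparisons between arms, i.e., intervention arms with control". The aim is given as "In order to achieve a test power of 80% and maintain family-wise error rate (FWER) of 0.05", and the result as "Bonferroni method for three comparisons, alpha of 0.017, and an estimated sample size of 370 pregnant women per arm was attained". The same paragraph also says that the size is "based on 1-tailed hypothesis testing of birth weight as the primary outcome, a significance level of 2.5% to account for multiple comparisons". The effect is stated ("it is assumed that the mean difference will be at least 100 g"), but no SD is given. Allocation is equal across the four arms ("treatment allocation ratio of 1:1:1:1").

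**The concern.** The F-test of a one-way ANOVA asks whether four means are all equal. The trial was sized to ask, three times, whether a given intervention arm gives heavier babies than control. The two differ in three ways:

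- F does not say which arm differs from control.
- F counts differences among the three supplement arms as evidence, although none of the sized comparisons concerns them.
- F has no direction and carries no 0.017 threshold, whereas the sizing is described as one-tailed.

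A model with covariates is also an ANCOVA, not a one-way ANOVA; that is only a matter of labelling.

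What is at stake is the decision rule for the primary outcome. As written, an analyst could report the F-test alone, use F as a gate before ordinary pairwise tests, or go straight to three contrasts at 0.017. These rules can name different arms as effective from the same data, and they do not share the same error rate.

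**Working it through.** **Inputs.** From the protocol article: difference 100 g, 370 evaluable women per arm, power 80%, FWER 0.05, three comparisons, levels 0.017 and 2.5%, one-tailed. Not given: the SD of birth weight.

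**1. The plan's own figure.** For two equal arms, n = 2 × SD² × (z_α + z_β)² / Δ². The figure of 370 cannot be checked forwards without the SD, so solve for it: SD = 100 × √(370/2) / (z_α + 0.842) = 1360.1 / (z_α + 0.842).

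| Level | z_α | SD implied by 370 per arm |
|---|---|---|
| 0.05/3, two-sided | 2.394 | 420 g |
| 0.017, two-sided | 2.387 | 421 g |
| 0.017, one-sided | 2.120 | 459 g |
| 0.025, one-sided | 1.960 | 485 g |

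An SD of 420 g returns exactly 370 at two-sided 0.05/3. It is an assumption chosen to match, so the 80% power it gives for Bonferroni is no independent confirmation. Read literally, one-tailed testing at 0.017 needs about 459 g.

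**2. Error rates by decision rule.** Simulation of 400,000 four-arm trials, 370 per arm, pooled variance on 4 × 369 = 1,476 degrees of freedom.

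No arm works (these rates do not depend on the SD):

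| Rule | Chance of any false claim |
|---|---|
| Omnibus F at 0.05 | 5.0% |
| Three control contrasts at 0.017 | 4.3% one-sided, 4.5% two-sided |
| Three contrasts at one-sided 0.025 | 6.2% |
| F as gate, then unadjusted two-sided 0.05 contrasts | 4.0% |
| Three unadjusted two-sided 0.05 contrasts, no gate | 12.5% |

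One arm truly +100 g, two null: F as gate followed by unadjusted two-sided 0.05 contrasts makes a false claim about a null arm in about 9% of trials. Bonferroni contrasts do so in 3.1%. The gate therefore protects when no arm works, but not when one does.

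**3. Do F and the contrasts agree?** With SD 420 g and two-sided contrasts at 0.0167, F at 0.05 is significant while no contrast passes in 12.5% of trials when one arm works, and in 0.1% when all three work. The same simulation at SD 459 g gives about 16% for one effective arm, or about 11% if the contrasts are one-sided, so the upper end moves with both unknowns.

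**4. What the choice of adjustment is worth.** At SD 420 g, two-sided, with all three arms at +100 g, power per arm is 80.0% with Bonferroni, about 81% with Dunnett and about 86.5% with Holm. With only one effective arm, Holm gives 80.1% against 80.0% for Bonferroni. All three hold FWER at 0.05.

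**5. Cost of changing sidedness.** If the one-tailed sizing is taken literally (SD 459 g), the standard error of a difference is 459 × √(2/370) = 33.75 g and 100/33.75 = 2.963. Two-sided testing at 0.0167 then has power Φ(2.963 − 2.394) = Φ(0.569), about 71%.

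**The case against.** A reader might infer that the trial fails to deliver its FWER of 0.05. The documents do not support that. The Sample size section states Bonferroni, three comparisons and FWER 0.05, and nothing in the Statistical analysis section withdraws them. A four-arm linear model supplies the three control contrasts directly, and the reference to mean differences under an adjusted model points that way, since an F-test alone yields no mean differences. Contrasts at 0.017 hold the error rate at about 4.5%. The 12.5% and 9% error rates belong to unadjusted follow-up tests, which the article never says it will use.

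It is also fair that a condensed article may leave contrast details to an analysis plan that is not shown, and that Holm in place of a valid Bonferroni rule is an improvement and not a correction. The disagreement between F and the contrasts almost vanishes when all three arms work, and it rests on an SD that the article does not give.

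All of this stands, and it limits the claim. It does not remove the point, because the article is not silent: it names a specific method, and the test that goes with that method is not the one the trial was sized for. Nor can the reader simply carry 0.017 across. The Sample size section also gives 2.5% as the level that accounts for multiplicity, and three one-sided tests at 0.025 would give about 6.2%.

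**Conclusion.** The point holds as a mismatch between the named analysis and the design hypothesis. The Statistical analysis section does not secure the FWER that the Sample size section promises, because contrasts, level, sidedness and any gating are left open beside an omnibus method. The size depends on what is then done: no inflation if the three contrasts are tested at 0.017, and about 9% with one effective and two null arms if unadjusted comparisons follow the F-test. F and the two-sided control contrasts at 0.0167 would point to different conclusions in about 0.1% to 12.5% of trials at an assumed SD of 420 g. The error rates with no effective arm do not rest on the SD; the disagreement and power figures do.

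**What to change.** Amend the Statistical analysis section, before the arms are unblinded, to say that:

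- the primary analysis is an ANCOVA of birth weight on arm, with the prespecified baseline covariates that the section lists;
- the three contrasts, each intervention arm minus control, are tested with Holm (or Dunnett, or at least the Bonferroni rule already stated) at FWER 0.05;
- mean differences are reported with Bonferroni or Dunnett confidence intervals;
- the omnibus F-test is descriptive and not a gate.

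In the Sample size section, state one sidedness and one level, reconciling one-tailed, 2.5% and 0.017, and give the SD used. If the chosen sidedness differs from that used for sizing, restate the power.

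The cost is about one paragraph and no new data. The present sample size can stay, but its power may have to be restated: moving to two-sided tests after a truly one-tailed sizing would leave about 71%. The downside of Holm is that its matching intervals are less simple, so a Bonferroni or Dunnett interval beside it may occasionally include zero when Holm rejects. Bonferroni alone would already cure the mismatch; Holm adds power when more than one arm works and loses none otherwise.
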